## Methods

### Aims

The main objective of the study is to evaluate the effectiveness of the school-based program #Tamojunto2.0 at 9 and 18 months of follow-up in the prevention of drug use (alcohol, tobacco, inhalants, marijuana, cocaine, crack and amphetamines) and binge drinking among Brazilian students. Our main hypothesis is that the #Tamojunto2.0 program will delay the first use of these drugs and will decrease the prevalence of use among students who participate in the intervention compared to the students in the control group.

The second objective of this study is to evaluate the effectiveness of the program at 9 and 18 months of follow-up in the prevention of school violence and psychiatric symptoms (depression, anxiety, *attention-deficit/hyperactivity disorder* and eating disorders) among Brazilian students. Our second hypothesis is that the #Tamojunto2.0 program will reduce the prevalence and incidence of secondary outcomes among students participating in the intervention compared to the students in the control group.

The third objective of the study is to evaluate the mediating effect of the skills taught by the program (decision-making skills, refusal skills, knowledge about drugs and beliefs about drugs) in reducing primary outcomes (alcohol, tobacco, marijuana, inhalant, cocaine, crack and amphetamine use and binge drinking) and secondary outcomes (reports of school violence and psychiatric symptoms), comparing the control and intervention groups at three different time points (0, 9 and 18 months). Our third hypothesis is that the improvement in the skills taught by the program will mediate the program’s effect on reducing the primary and secondary outcomes, as described by a logical model.

Finally, the fourth objective of the present study is to evaluate the program implementation fidelity to identify possible changes in the original content and to measure if the dose of the program offered to the students influences the effects of the program. Our fourth hypothesis is that the greater the dose of the program offered to the students and the smaller the changes to the original content are, the greater the effect of the program in the prevention of the proposed outcomes will be.

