### Study design

A randomized controlled trial with two parallel groups (intervention and control) will be conducted to evaluate the effectiveness of the program for adolescents enrolled in 8th grade middle school in 70 public schools in three Brazilian cities, totaling approximately 6300 students distributed in 210 groups. Randomization will be conducted at the school level. Schools randomly selected to be part of the intervention group will offer the 12 lesson #Tamojunto2.0 program in the year 2019. Schools in the control group will not offer prevention programs or activities in 2019. The selection of schools and the allocation to the control or intervention group will be performed by a simple random draw from the list of the National Institute for Educational Studies and Research ‘Anísio Teixeira’ (INEP), which includes all schools from each municipality.

The baseline data (T1) will be collected two weeks before implementation of the program in February/March 2019, and the follow-up data will be collected at 9 months (T2) in November/December 2019 and at 18 months (T3), August/September 2020 after the initial data collection in August 2020. The data will be collected simultaneously for both groups. This protocol was prepared in accordance with SPIRIT 2013 [22], and the study will be conducted according to the CONSORT guidelines [23].

At the end of each lesson, all teachers in the experimental classes will complete a fidelity and dose form, stating which of the planned activities were or were not taught in the lesson and if the teacher made any changes. Figure 1 shows the study design flowchart.

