### Mediators

As mediators of program effectiveness, the following will be evaluated: 1. normative beliefs; 2. positive beliefs and negative beliefs about alcohol and marijuana use; 3. knowledge about drugs; 4. decision-making skills; and 5. refusal skills [34]. The scales for each mediator are described in Table 1.

In addition to the modules covering primary outcomes, secondary outcomes and mediators, the questionnaire also has a module on sociodemographic data. The socioeconomic class will be evaluated through the ABEP (Brazilian Market Research Association) scale [35] (Table 1**).**

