### Data analysis of the randomized controlled trial

The data will initially be analyzed by a descriptive analysis, that is, qualitative variables will be summarized as numbers and percentages and numerical variables as means, standard deviations, medians, minima and maxima. Descriptive analyses will be performed for different patterns of drug use. This dataset will be used to calculate sample weights through the svy command in Stata so that the baseline data analysis can be presented in an expanded form, aiming at correcting for losses and extrapolating the data to the sample universe [39, 40].

All analyses will be carried out in the two samples: “intention to treat” (ITT), which will include all the participating classes that received at least one lesson of the program, and “per protocol” (PP). The PP analysis will include only those classes that receive the complete protocol (12 lessons), determined based on evaluating the dose and fidelity form that will be completed by the teacher at the end of each lesson.

Because the data are collected in groups, they are not independent at two levels (school and class), and the measures of association should be analyzed through GLLAMM (Generalized Linear Latent and Mixed Models), which calculates the level of dependence between the data [41]. Due to the hierarchical structure of the data, multilevel models will be used to simultaneously test for differences in the prevalence of outcomes between times and between groups, considering schools as a modeling level (Gllamm Stata 14). All analyses will be adjusted by sex, socioeconomic level and site. The analyses will be performed in Stata 15 (descriptive analyses and multilevel GLLAMM), and a significance level of 5% will be adopted.

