Structural equation modeling (SEM) will be used to analyze the mediators involved in reducing the primary and secondary outcomes over 18 months [42] (Fig. 2) and to assess the effectiveness of the intervention in changing the behavioral patterns of adolescents related to drug use and violence through latent transition analysis (LTA). LTA can be understood as a longitudinal extension of latent class analysis, as it is used to identify and describe the ideal number of classes representing the study population, following their transition over a given period [43]. This approach offers great advantages compared to traditional logistic regression methods in longitudinal studies, such as a lower rate of false discovery compared to multilevel logistic regression models when assessing the effects of an intervention on multiple outcomes [44]. Drug use is often studied with the latent class model due to the high correlation observed between the different drugs used, addressing the heterogeneity of drug use behavior in adolescents [45]. These analyses will be performed with the Mplus 8 software, and a significance level of 5% will be adopted.

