**Fig. 2 Fig2:**
[figure not shown]
Mediation model for the outcomes of students participating in the evaluation of the #Tamojunto2.0. program; Three mediation models will be generated using the outcome variables of drug use in the past year and in the past month and incidence of drug use

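### The visible text names only sex, socioeconomic level and site as covariates, and nothing puts baseline skills or baseline drug use into the mediator-to-outcome part of the mediation models

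*Protocol article*

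**What the plan says.** All references are to the protocol article.

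- **Covariates.** Under Data analysis of the randomized controlled trial, after the multilevel models are described: "All analyses will be adjusted by sex, socioeconomic level and site".
- **Mediation method.** The next paragraph, under the same heading: "Structural equation modeling (SEM) will be used to analyze the mediators involved in reducing the primary and secondary outcomes over 18 months". It names Mplus 8 and a 5% significance level, and no covariates.
- **Mediation outcomes.** The Fig. 2 caption announces three models, for "drug use in the past year and in the past month and incidence of drug use". The diagram itself is not in the text available for this review.
- **Hypothesis.** Under Aims: "Our third hypothesis is that the improvement in the skills taught by the program will mediate" the effect on the outcomes. The objective is described as "comparing the control and intervention groups at three different time points (0, 9 and 18 months".
- **Mediators.** The Mediators section lists normative beliefs, positive and negative beliefs, and "3. knowledge about drugs; 4. decision-making skills; and 5. refusal skills".
- **Baseline.** Under Study design: "The baseline data (T1) will be collected two weeks before implementation of the program in February/March 2019". Table 1 places drug use, skills and beliefs in the same student questionnaire. It labels socioeconomic class, age and sex as confounders, and skills and beliefs only as mediators.

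**The concern.** A mediation model has two links. Randomisation protects the link from program to skill, and it protects the total effect of the program. It does not protect the link from skill to drug use, because students are not randomised to skill levels. A student who already drinks or smokes at T1 may already hold more favourable beliefs and weaker refusal skills. If both traits persist, follow-up skill and follow-up use are correlated even when skill has no effect on use. Sex, socioeconomic level and site do not remove such a correlation.

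There is also a mismatch of question. Improvement is a change from T1. A model that uses follow-up skill without T1 skill relates the level of skill to drug use, which is not what hypothesis 3 says.

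At stake is the claim about mechanism. The Strengths and limitations section presents the mediator analysis as a way to learn how the intervention works. The Background attributes the harm seen with the previous program version to how the alcohol content was adapted. A mediator credited falsely could send the next revision to the wrong component.

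**Working it through.** The plan gives no figure for the mediation analysis, so there is none to reproduce. The only input taken from it is the size: 35 schools x 90 students x 2 arms = 6,300. Everything else below is assumed, because the documents give no correlations, stabilities or program effect on skills.

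**Step 1: is a T1 term stated anywhere?** The covariate sentence has none. The structural equation paragraph has none. The Fig. 2 caption names outcomes only. The third objective names time 0, but as a comparison between arms, which does not place T1 values in the skill-to-use equation.

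**Step 2: the bias when skill truly has no effect.** Take standardised variables, with r0 the T1 skill-use correlation, s the stability of skill, t the stability of use and a the program effect on skill in SD units. Then:

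- follow-up skill = a x arm + s x (T1 skill) + noise
- follow-up use = t x (T1 use) + noise

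Within arm, the covariance of follow-up skill and follow-up use is s x t x r0. With unit variances this is also the fitted coefficient b. At r0 = -0.2 and s = t = 0.5, b = 0.5 x 0.5 x (-0.2) = -0.05, while the truth is 0.

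**Step 3: is that detectable?** With n = 6,300, SE(b) is about 1/sqrt(6300) = 0.0126, so |z_b| = 0.05/0.0126 = 3.97. With a = 0.10, SE(a) is about 2/sqrt(6300) = 0.0252, so z_a = 0.10/0.0252 = 3.97. The Sobel statistic for a x b is about 1/sqrt(1/3.97² + 1/3.97²) = 2.81, above 1.96. A false finding of mediation is the expected result in this case.

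**Step 4: simulation.** Linear models, 6,300 students, a = 0.10, true b = 0, Sobel test, 24 combinations of r0, s and t with 150 runs each. Selected rows:

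| r0 | s | t | b without T1 terms | false mediation without T1 | false mediation with T1 |
|---|---|---|---|---|---|
| -0.1 | 0.3 | 0.3 | -0.009 | 5% | 2% |
| -0.1 | 0.5 | 0.5 | -0.024 | 35% | 3% |
| -0.2 | 0.5 | 0.5 | -0.048 | 89% | 3% |
| -0.3 | 0.5 | 0.5 | -0.073 | 98% | 1% |
| -0.4 | 0.7 | 0.5 | -0.141 | 99% | 6% |

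Over all 24 cells the rate was 5% to 99% without T1 terms and 1% to 6% with them. The Monte Carlo standard error at a 5% rate is sqrt(0.05 x 0.95/150) = 1.8 percentage points.

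**Step 5: a version closer to the trial.** 70 schools of 90 students, intraclass correlation 0.005, a 10% binary outcome, program effect 0.2 SD (assumed), stabilities 0.4 to 0.6, cluster-robust tests with 68 df, both links required at p<0.05. False mediation was 11-32% at r0 = -0.1, 27-92% at -0.2 and 63-100% at -0.3. With the T1 mediator and yes/no T1 use added it was 4-7%.

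**Step 6: a necessary condition.** With a = 0 (r0 = -0.3, s = t = 0.5, 400 runs), the rate without T1 terms was about 4%, although b was still biased (-0.076). The false indirect effect arises only if the program moves the skill.

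**The case against.** The strongest reply is that the text is silent on T1 terms in these models and does not exclude them.

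- The covariate sentence stands among the multilevel-model sentences and is followed by the Stata software sentence. The structural equation paragraph has its own software and significance level, so the list may be meant for the multilevel models only.
- The mediation model is drawn in Fig. 2, which is not shown. Its absence here is not a fault of the plan, and T1 paths would normally be drawn there.
- The third objective names time 0 and improvement, which suggests that T1 is used in some form.
- A journal article commonly leaves the detail of secondary models to a fuller document.

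Most of this stands. A reader might infer that the plan leaves T1 skills and T1 drug use out of the mediation models. The documents do not support that as a certainty. What survives is narrower. The one covariate statement says that it covers all analyses, it sits under the heading that also covers the structural equation models, and no visible text adds T1 terms to the skill-to-use equation. Someone following the visible text literally would fit the confounded model.

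Two further points against are right. The incidence model counts new cases, so T1 use of that drug is dealt with by design. The near-nominal rates after adjustment are partly built in, because the simulated confounding runs only through the T1 measures.

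**Conclusion.** The point holds as a gap in the visible text that should be closed, for the mediation objective only. If the program shifts a skill or belief, and T1 terms are absent, a skill-use association that predates the program can be reported as mediation. The past-year and past-month models carry this in full. The incidence model carries it through T1 skills and T1 use of other drugs.

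The size cannot be stated for this trial. The range of about 5% to nearly 100% rests on assumed correlations (-0.1 to -0.4), assumed stabilities and an assumed nonzero program effect on skills. It shows that small prior associations suffice at this sample size, and it does not predict an error rate.

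A reader might also infer that the effectiveness results are biased. They are not, on this ground. Randomisation protects the total effect, the multilevel models compare arms across times, and the latent transition analysis models change from T1 status.

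**What to change.** In the structural equation paragraph, state that each mediation model includes the student's T1 value of the mediator or mediators and T1 drug use as predictors of both the mediator and the outcome, in addition to sex, socioeconomic level and site. For the incidence model, specify T1 mediators and T1 use of other drugs. If Fig. 2 already contains these paths, say so in the text and limit the covariate sentence to the multilevel (GLLAMM) models.

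The cost is one sentence and covariates already in the T1 questionnaire, with no new data collection. Students whose T1 questionnaire cannot be linked through the secret code will need missing-covariate handling. Unmeasured confounding of the mediator-to-outcome link remains after this change.

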**Fig. 2 Fig2:**
[figure not shown]
Mediation model for the outcomes of students participating in the evaluation of the #Tamojunto2.0. program; Three mediation models will be generated using the outcome variables of drug use in the past year and in the past month and incidence of drug use

### Dose and Fidelity evaluation data analysis

Quantitative data will be analyzed using the Stata 14 software using descriptive statistics, considering frequencies and prevalence. Inferential statistics will be applied to test hypotheses of differences between observations and observers.

The qualitative data will be transcribed in full and categorized according to their content similarity. The computer software NVivo version 10 will be used for the qualitative analysis [46].

## Trial status

By the time of this submission (February/2019), the study is in the recruitment and agreement phase with the selected schools.

## Discussion

This study protocol describes a randomized controlled trial to evaluate the effectiveness of the school-based drug prevention program #Tamojunto 2.0. The main objective of this study is to evaluate the effectiveness of the intervention in terms of drug use outcomes among Brazilian students. Data on school violence, psychiatric symptoms, and mediators of the program’s effectiveness, such as decision-making skills, refusal skills and knowledge and beliefs about drugs, will also be collected.

### Strengths and limitations

One of the strengths of this study is that it will include a representative sample of students from Brazilian public schools (*n* = 6300), obtained through a simple random draw of schools from the universe of schools in each municipality. In addition, this study will have three data collection points over time and can thus assess possible short-term and long-term effects of the program and enable more sophisticated analyses, such as mediation analysis and latent class transition analysis. Third, the study will use a school randomization design, which minimizes the effects of contamination that can occur in a project that randomizes the classes within each school. An additional strength of the study is that—in contrast to most RCT studies—we will focus not only on the effectiveness of the program but also on the mediators of change, which will shed light on how the intervention works and enable the proposal of possible mechanisms of action, as has already occurred in a pilot manner by the research group itself [16].

To contribute to the understanding of the intervention results, the present study will examine whether the intervention was implemented according to the original plan and the dose received in each participating class through the use of a dose and fidelity evaluation. The dose received in the implementation and the fidelity (i.e., how closely the program follows the original curriculum) are elements related to the expected outcomes of the program [47]. In this way, the study will identify the real conditions of the program implementation in the Brazilian public education system. Given the results obtained by Sanchez et al. [16], showing that the first version of the adaptation of the Unplugged program in Brazil resulted in a 30% increase in alcohol initiation by students, and considering the important changes made to the material to reverse this effect, it is important to evaluate whether 1) removing the components with a possible iatrogenic effect from the alcohol lesson was truly effective and 2) whether the lessons are being taught exactly as described in the handbooks provided to the teachers and students.

Some limitations of this study must be noted. The main limitation is related to the known high rate of school absences of the Brazilian student population, which could result in bias. However, this is a common limitation to longitudinal studies [48–50], and the goal is to try to minimize it by giving prior notice to the students about the researchers’ visit for data collection, which did not occur in previous versions of the study [16]. Another limitation of the study is that the information is obtained through self-reporting by the students themselves. Although this method may lead to measurement bias, self-reporting is the most recommended evaluation method for adolescents and has been found to have excellent validity in studies evaluating drug-related behaviors [51, 52]. Currently, there are no viable alternatives for collecting data on alcohol use in adolescent samples, as biological measures would not be appropriate in a sample in the early stages of alcohol use [53]. To avoid the overreporting of drug use, a question of the use of fictitious drugs (holoten and carpinol) has been added to the questionnaire to screen this problem. In cases where the student responds positively to these drugs, the questionnaire will be excluded from the study, reducing the information bias [54].

## Conclusion

Considering the iatrogenic results of the first version of #Tamojunto, a new adaptation of the material was carried out to better reflect the original content of Unplugged, which has already shown positive preventive results in the European context. Thus, a randomized controlled trial protocol with the inclusion of implementation dose and fidelity measures was designed to evaluate the effectiveness of the new version of the program that will be applied by the Brazilian government, now titled #Tamojunto 2.0. Considering that the #Tamojunto 2.0. program was developed with the aim of being applied as a universal intervention, within a context of a national public policy, we believe that this study will contribute to supporting decision-making regarding the dissemination of the new version of this program in Brazilian public schools.

## Data Availability

Not applicable.

## Abbreviations

ABEP: Brazilian Market Research Association
BMH: Brazilian Ministry of Health
EU-DAP: European Drug Addiction Prevention Trial
GLLAMM: Generalized Linear Latent and Mixed Models
INEP: National Institute for Educational Studies and Research ‘Anísio Teixeira’
ITT: Intention To Treat
LTA: Latent Transition Analysis
PP: Per Protocol
RCT: randomized controlled trial
SEM: Structural equation modeling
UNODC: United Nations Office on Drugs and Crime
